# Clinical Efficacy and Safety of the Herbal Prescription, HH333, in Preventing Recurrent Stroke in Patients With Ischemic Stroke Induced by Small-Vessel Disease: Protocol for Multicenter, Double-Blind, Randomized, Prospective, Pilot Clinical Trial

**DOI:** 10.2196/70953

**Published:** 2025-05-13

**Keywords:** HH333, ischemic stroke, herbal medicine, randomized controlled trial, protocol

## Abstract

**Background:**

Patients with ischemic stroke are at high risk of recurrence, making preventive care an important factor. Current antiplatelet therapy for recurrence prevention treatment has several limitations. Recent retrospective observational studies suggested that HH333, an herbal prescription, has an inhibitory effect on stroke recurrence in small-vessel diseases.

**Objective:**

This study aims to propose a protocol for evaluating the efficacy and safety of HH333 in patients with ischemic stroke induced by small-vessel disease.

**Methods:**

In this multicenter, double-blind, randomized, prospective, pilot clinical trial, 236 patients from 3 university Korean medicine hospitals in South Korea with ischemic stroke caused by small-vessel disease will be recruited and randomly assigned to either the HH333 or the placebo group. Both patients and investigators will be blinded to prevent access to the allocation results. The HH333 group will take 2 capsules of HH333 once daily for 720 days, whereas the placebo group will take HH333 placebo capsules in the same manner. Efficacy will be assessed using the recurrence rate of ischemic stroke, which will be assessed on days 30, 90, 180, 270, 360, 450, 540, 630, 720, and 750 after starting the medication. The effects on quality of life and fatigue with the Fatigue Severity Scale (FSS), Fatigue Assessment Scale (FAS), and Korean Patient Health Questionnaire (K-PHQ-9), functional improvement with Korean National Institutes of Health Stroke Scale (K-NIHSS), modified Rankin Scale (mRS), Korean modified Barthel Index (K-mBI), and Korean Montreal Cognitive Assessment (K-MoCA) and Pattern Identification also will be evaluated on days 0, 90, 180, 270, 360, 450, 540, 630, and 720 after starting the medication. Safety will be evaluated by performing blood and urine tests and electrocardiography on days 30, 90, 180, 270, 360, 450, 540, 630, and 720 after starting the medication.

**Results:**

Recruitment for the study started on May 22, 2024, and is scheduled to end on November 30, 2026. As of November 13, 2024, a total of 12 participants have been randomized.

**Conclusions:**

The protocol will provide a detailed process for a clinical trial evaluating the efficacy of preventing recurrent ischemic stroke caused by small-vessel disease and improving neurologic symptoms and the safety of HH333 in ischemic stroke. The results of this study provide a basis for alternative treatments to prevent and treat ischemic stroke.

**Trial Registration:**

Clinical Research Information Service KCT0009431; https://tinyurl.com/y2ctvje8

**International Registered Report Identifier (IRRID):**

DERR1-10.2196/70953

## Introduction

Patients with ischemic stroke are at high risk for recurrence [1]. Generally, ischemic stroke recurrence rates over 5 years range from 10% to 53% [2]. Recurrent stroke is associated with twice the risk of death and worse functional outcomes compared to patients with first-time stroke [3]. It also costs twice as much as hospitalization for a first-time stroke [4].

Antiplatelet or anticoagulant therapy is currently recommended as the first-line treatment for the prevention of recurrent ischemic stroke [5]. However, there are differences in the pathogenesis of ischemic stroke between Western and Asian populations, with Northeast Asians such as Koreans, Chinese, and Japanese having a higher proportion of strokes caused by small-vessel disease than Westerners [6,7]. Ischemic stroke induced by small-vessel disease usually results from the gradual thickening of the vessel wall caused by hypertension and is more likely to be accompanied by intracerebral microbleeds [8]. This may limit the use of antiplatelet or anticoagulant medications that may increase the bleeding propensity. HH333 is a complex herbal medicine that has inhibitory effects on coenzyme A reductase and pancreatic lipase [9], antioxidant and anti-inflammatory effects through suppression of nitric oxide biosynthesis and prostaglandin E2 [10], antihyperlipidemic and anti-inflammatory effects through activation of nitric oxide production [11], and endothelial cell proliferation through activation of MAP kinase [12]. Previous clinical studies have reported antihypertensive effects in stroke patients with hypertension [13], antilipidemic effects in patients with hypercholesterolemia [14], immediately improving cerebral blood flow in normal subjects [15], and improvement in arterial stiffness in patients with increased pulse wave velocity [16]. Based on these effects, HH333 is a promising medication for cerebrovascular and cardiovascular disease [17].

Specifically, HH333 inhibits the progression of microangiopathy, a key factor in small-vessel disease, and thus prevents the recurrence of ischemic stroke induced by small-vessel disease with a 2-year recurrence rate was 1.12%-2.02% [18-20], which is less than conventional antiplatelet agents [21-24]. Regarding safety, a previous retrospective study showed that the incidence of adverse events with HH333 was 2.0%, with no serious adverse events (SAEs) [25]. However, since these studies were all single-arm retrospective observational studies, there is no comparative analysis with a control group, and the data rely on medical records, which can be inaccurate. Therefore, there is a need for prospective clinical studies with a control group to rationalize and better understand these findings.

We present a protocol for a randomized controlled clinical trial to validate the clinical efficacy and safety of HH333 in patients with ischemic stroke induced by small-vessel disease. This study aimed to provide a high level of evidence for the efficacy of HH333 in ischemic stroke and ultimately propose a novel alternative for stroke treatment.

## Methods

### Study Design

This multicenter, double-blind, randomized controlled trial (RCT) aimed to assess the prevention of recurrent ischemic stroke and the safety of HH333 in patients with ischemic stroke induced by small-vessel disease. It was conducted at 3 university Korean medicine hospitals in South Korea: Kyung Hee University Korean Medicine Hospital, Dongguk University Ilsan Korean Medicine Hospital, Wonkwang University Gwangju Korean Medicine Hospital. Within 90 days of onset at baseline, patients will receive HH333 or a placebo, 2 capsules (800 mg) at a time, once a day for 720 days. The clinical effect of HH333 will be evaluated by ischemic stroke recurrence, which is the primary efficacy endpoint, at baseline and on days 30, 90, 180, 270, 360, 450, 540, 630, 720, and 750 after starting the medication. Total scores on the Fatigue Severity Scale (FSS), Fatigue Assessment Scale (FAS), Korean Patient Health Questionnaire (K-PHQ-9), and the probability of each type of Pattern Identification (fire heat, dampness-phlegm, qi deficiency or yin deficiency) will be evaluated as secondary efficacy endpoints at baseline and 90, 180, 270, 360, 450, 540, 630, and 720 days after starting medication. The total scores on the Korean National Institutes of Health Stroke Scale (K-NIHSS), modified Rankin Scale (mRS), Korean Modified Barthel Index (K-mBI), and Korean Montreal Cognitive Assessment (K-MoCA) will also be measured as exploratory endpoints at the same time as the secondary efficacy endpoints. The safety of HH333 will be assessed based on the presence of adverse events at the same time as the primary efficacy endpoints. The enrollment, interventions, and assessments of the study are summarized in Table 1. A schematic of the study process is shown in Figure 1.

**Table 1 table1:** Schedule of enrollment, interventions, and assessments.

Visit	0	1	2	3	4	5	6	7	8	9	10	11^a^	UV^b^
Day	–14^c^	0	25-35	80-100	165-195	255-285	345-375	435-465	525-555	615-645	705-735	745-755	
Informed consent	✓												
Demographic information^d^	✓												
Medical history^e^	✓												
History of ischemic stroke^f^	✓												
Medications^g^	✓												
Physical examination	✓	✓	✓	✓	✓	✓	✓	✓	✓	✓	✓		If needed
Vital sign	✓	✓	✓	✓	✓	✓	✓	✓	✓	✓	✓		If needed
Physical measurements	✓												
Laboratory tests^h^	✓												
Electrocardiogram	✓		✓	✓	✓	✓	✓	✓	✓	✓	✓		If needed
Evaluating inclusion and exclusion criteria	✓												
Randomized allocation		✓											
Experiment medication administration		✓	✓	✓	✓	✓	✓	✓	✓	✓	✓		
Medication adherence^i^			✓	✓	✓	✓	✓	✓	✓	✓	✓		If needed
Concomitant treatment		✓	✓	✓	✓	✓	✓	✓	✓	✓	✓	✓	If needed
Primary efficacy endpoint: recurrence of ischemic stroke			✓	✓	✓	✓	✓	✓	✓	✓	✓	✓	If needed
Secondary efficacy endpoints^j^		✓		✓	✓	✓	✓	✓	✓	✓	✓		If needed
Exploratory endpoints^k^		✓		✓	✓	✓	✓	✓	✓	✓	✓		If needed
Safety assessments^l^			✓	✓	✓	✓	✓	✓	✓	✓	✓		If needed
Adverse events^m^		✓	✓	✓	✓	✓	✓	✓	✓	✓	✓	✓	

^a^Telephone investigation.

^b^UV: Unscheduled visit. Visiting on a day other than the original visit schedule due to an adverse event, etc.

^c^Screening performed within 14 days of informed consent.

^d^Age, sex, smoking, and alcohol history.

^e^Within 1 year prior to visit 0.

^f^Time of first onset and diagnosis (including year, month, and day if possible), date of computed tomography or magnetic resonance imaging, ischemic stroke territory, Trial of Org 10172 in Acute Stroke Treatment classification, history of stroke-related surgery, stroke risk factors, and stroke-related symptoms.

^g^Within 4 weeks prior to visit 0.

^h^Complete blood count (red blood cell, hemoglobin, hematocrit, platelet, white blood cell); biochemistry (fasting blood glucose, blood urea nitrogen, creatinine, natrium, potassium, chloride, aspartate aminotransferase, alanine aminotransferase, C-reactive protein, calcium, uric acid); urine human chorionic gonadotropin for women of childbearing age, excluding sterilization and menopause (more than 12 months since last menstrual period); premature menopause before the age of 40 years, follicle-stimulating hormone test for differential diagnosis.

^i^Drop out if <80%.

^j^Total scores of Fatigue Severity Scale (FSS), Fatigue Assessment Scale (FAS), Korean Patient Health Questionnaire (K-PHQ-9), and probability of each type of Pattern Identification (fire heat, dampness-phlegm, Qi deficiency, and Yin deficiency).

^k^Total scores of the Korean National Institutes of Health Stroke Scale (K-NIHSS), Korean modified Rankin Scale (K-mRS), Korean modified Barthel Index (K-mBI), Korean Montreal Cognitive Assessment (K-MoCA).

^l^Complete blood count (red blood cell, hemoglobin, hematocrit, platelet, white blood cell); biochemistry (fasting blood glucose, blood urea nitrogen, creatinine, natrium, potassium, chloride, aspartate aminotransferase, alanine aminotransferase, C-reactive protein, calcium, uric acid); urine tests (specific gravity, pH, albumin or protein, glucose, ketone, bilirubin, occult blood, urobilinogen, nitrite, leukocyte, human chorionic gonadotropin for women of childbearing age); electrocardiogram; hemorrhage events (cerebral hemorrhage, gastrointestinal bleeding, etc) related to antiplatelet or anticoagulant; vital sign; physical examination.

^m^Self-reported by the participant or judged by the investigator.

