**Inclusion criteria**
Men and women aged 19 to 80 years.Diagnosed with ischemic stroke induced by small-vessel disease in the Trial of Org 10172 in Acute Stroke Treatment (TOAST) classification within 90 days of screening based on new neurologic and brain imaging (computed tomography or magnetic resonance) findings to support them.Participants had no communication problems and voluntarily agreed to participate.

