**Exclusion criteria**
Diagnosis of degenerative brain diseases (eg, Parkinson’s disease, Alzheimer disease, etc).Have a brain condition other than ischemic stroke (eg, brain tumor, traumatic brain injury, arteriovenous malformation, Moyamoya disease, and stroke due to these conditions).Unstable vital signs at screening (eg, systolic blood pressure greater than 160 mm Hg despite taking blood pressure medications).Serious medical condition (eg, liver cirrhosis, chronic kidney disease stage V, or severe heart failure of New York Heart Association (NYHA) grade III or greater).History of malignancy, including leukemia and lymphoma, within the past 5 years.Hepatic and renal dysfunctions.Aspartate aminotransferase, alanine aminotransferase ≥2 times the upper limit of normal at screening.An estimated glomerular filtration rate < 60 mL/min/1.73 m2 at screening.Within 24 hours of onset.Patients with Korean National Institutes of Health Stroke Scale (K-NIHSS) score 21 to 42.Pregnant, nurses, or women of childbearing potential who have negative pregnancy test results and have not agreed to use contraception during the study.Previously experienced hypersensitivity after taking HH333’s constituent medicines *Scutellariae radix*, *Coptidis rhizoma*, *Phellodendri cortex*, *Gardeniae fructus*, and *Rhei rhizoma*.Any other study medications administered within 30 days prior to screening.Patients who have not been administered the study medication or who have participated in a simple observational clinical trial are eligible.Difficulty taking the doses required in this study.Judged by the investigator as nonconformity for participation in the trial for any reason.Plans to use anticoagulants during the study or have difficulty discontinuing them.

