### Exploratory Endpoints: K-NIHSS, mRS, K-mBI, and K-MoCA

The NIHSS is a tool for assessing neurological deficits resulting from stroke developed by the National Institutes of Health [32] and is currently the most widely used tool for stroke severity assessment, with a Korean version validated and used [33]. It comprises 15 questions in 11 checkpoints, each of which is scored on a scale of 0 to 4, with a total score calculated, with higher scores indicating higher severity. The mRS is a tool developed by van Swieten et al to assess the degree of disability in patients with stroke [34] and is currently the most widely used stroke functional assessment scale [35]. It is rated on a scale of 0 to 6, with higher scores indicating more severe impairment. The mBI is a tool to assess independence in activities of daily living after stroke developed by Shah et al [36], and translated with validation in Korean [37]. It contains 10 questions, each rated on a scale of 0 to 5, 0 to 10, or 0 to 15, with a higher total score indicating a lower dependency. The MoCA is a tool that examines cognitive function and was originally developed to identify mild cognitive impairment [38] but is now widely used for cognitive impairment caused by stroke, and the Korean version has been validated and used [39]. It consists of visuospatial and executive (5 points), naming (2 points), attention (6 points), language (3 points), abstraction (2 points), delayed recall (5 points) and orientation (6 points). The perfect score is 30, with a higher total score indicating higher cognitive function. Investigations were conducted during the administration period on days 0 (baseline), 90, 180, 270, 360, 450, 540, 630, and 720.

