#### Analysis of Secondary Efficacy and Exploratory Endpoints

Secondary efficacy endpoints that FSS, FAS, K-PHQ-9 total score change, each pattern identification probability change, and exploratory endpoints K-NIHSS, mRS, K-mBI, K-MoCA total score change are continuous variables, and the average for each measurement, SD, median, minimum value, maximum value will be presented and the difference between the HH333 group and the control group will be tested using repeated measures ANOVA.

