Based on this evidence, the Korean Medicine Clinical Practice Guideline for Stroke, compiled by the Korean Ministry of Health and Welfare, recommends that HHT, the main component of HH333, may be considered for the treatment of ischemic stroke to improve neurological disability and prevent recurrence [56]. However, the recommendation is graded as C/Low because clinical studies of HH333 have only been conducted on hypertension and hyperlipidemia, which are risk factors for ischemic stroke, and experimental studies, literature reviews, or retrospective cohort studies on ischemic stroke, which are not sufficient for high quality. In modern clinical research, RCTs represent the highest level of evidence in evidence-based medicine, and significant results from RCTs are more conclusive than other types of clinical research information [57]. Therefore, in order to realize the possibility of HH333 as a therapeutic and recurrent prevention agent for ischemic stroke by improving the quality of evidence, we present a double-blind RCT compared with a placebo to evaluate the clinical effectiveness and safety of HH333 for ischemic stroke in patients with ischemia induced by small-vessel disease.

A limitation of this protocol is that it excluded patients at high risk of bleeding, such as those taking anticoagulants. This exclusion was made because it was important to exclude any factors that could influence bleeding propensity in this study, but it may limit the generalizability of the results.

We hypothesized that HH333 would be effective and safe in preventing recurrent ischemic stroke and improving neurological symptoms in patients with small-vessel disease induced by ischemic stroke. This clinical study will generate data on the therapeutic efficacy and safety of HH333 in ischemic stroke. If the results of this study prove the efficacy and safety of HH333, they will serve as a basis for further use of HH333 with ischemic stroke and will also contribute to the development of novel alternatives for the treatment and prevention of ischemic stroke.

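### The 90-day entry window runs on two different clocks, and the significance-triggered covariate rule leaves a wide spread in time since stroke unadjusted in the change-score analyses

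*Protocol article*

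**What the plan says.** **Entry window.** The Study Design section of the protocol article reads: "Within 90 days of onset at baseline, patients will receive HH333 or a placebo". That clock starts at onset and stops at baseline. The inclusion criteria in Textbox 1 require a TOAST small-vessel diagnosis "within 90 days of screening based on new neurologic and brain imaging" findings, a clock that starts at diagnosis and stops at screening. Table 1 places screening (visit 0) at day -14 and randomisation (visit 1) at day 0. Its footnote c reads "Screening performed within 14 days of informed consent". The lower limit is an exclusion criterion: "Within 24 hours of onset".

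**Functional scores.** For K-NIHSS, mRS, K-mBI and K-MoCA the schedule is: "Investigations were conducted during the administration period on days 0 (baseline), 90, 180, 270, 360, 450, 540, 630, and 720". The analysis section states that the "exploratory endpoints K-NIHSS, mRS, K-mBI, K-MoCA total score change are continuous variables", and that "the difference between the HH333 group and the control group will be tested using repeated measures ANOVA". FSS, FAS and K-PHQ-9 are handled in the same way as secondary endpoints. No term for time since stroke is named.

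**Covariates.** Under Demographic Information Analysis, a baseline item becomes a covariate in the efficacy analysis only if it was found to differ significantly between the two groups. Footnote f of Table 1 shows that dates of first onset and diagnosis are recorded at visit 0, with the day given where possible.

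**The concern.** There are two separate matters.

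First, both ends of the entry window differ between the two statements: onset against diagnosis, and baseline against screening. A patient near the limit can satisfy one and fail the other, and three sites could read the rule differently.

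Second, whichever clock applies, one patient may have the day-0 assessment within days of the stroke and another about three months after it. The first has most spontaneous recovery still ahead, and it will be counted as change from day 0. The second has little left. This variation between patients is partly predictable from the time of entry and the day-0 score. The covariate rule nevertheless admits such variables only when the arms happen to differ on them. What is at stake is the precision of the functional and fatigue comparisons.

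**Working it through.** **1. The two windows side by side.**

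- Study Design: day 0 minus onset is at most 90 days.
- Textbox 1: screening minus diagnosis is at most 90 days.
- Table 1: day 0 minus screening is up to 14 days. This comes from the day -14 column; footnote c alone only ties screening to consent.

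Upper limit for day 0 under Textbox 1, taking diagnosis date as onset date: 90 + 14 = 104 days, or more if diagnosis came after onset. Under Study Design it is 90 days. The lower limit is just over 1 day in both.

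The windows are nested. Diagnosis is not before onset and screening is not after day 0, so (screening - diagnosis) ≤ (day 0 - onset). Anyone within 90 days under Study Design therefore also meets Textbox 1. Disagreement is confined to about days 91-104. For example, a patient diagnosed 85 days before screening and randomised 14 days later meets Textbox 1, but is at 85 + 14 = 99 days and outside the Study Design limit.

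**2. How often the covariate rule would adjust for entry time.** Under randomisation, a baseline variable differs significantly at the protocol's 5% level in about 5% of trials, whatever its prognostic strength. Entry time and the day-0 score would thus each stay out of the model in about 95% of trials.

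**3. Size of the loss from entry time alone.** The protocol gives no recovery curve and no SD, so these are assumptions:

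- recovery still to come at entry time t is R·exp(-t/τ), with R the total spontaneous recovery in units of the residual SD of change;
- t is uniform from day 1 to the limit;
- τ is 20, 30 or 60 days.

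Unadjusted variance relative to residual variance is 1 + R²·Var[exp(-t/τ)].

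| Limit | τ (days) | SD of exp(-t/τ) | R = 0.5 | R = 1 | R = 2 |
|---|---|---|---|---|---|
| 90 | 20 | 0.239 | 1.014 | 1.057 | 1.228 |
| 90 | 30 | 0.248 | 1.015 | 1.062 | 1.246 |
| 90 | 60 | 0.216 | 1.012 | 1.046 | 1.186 |
| 104 | 20 | 0.233 | 1.014 | 1.054 | 1.217 |
| 104 | 30 | 0.249 | 1.015 | 1.062 | 1.247 |
| 104 | 60 | 0.227 | 1.013 | 1.052 | 1.207 |

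Example: τ = 30, R = 2, limit 90 gives 1 + 4 × 0.248² = 1.246.

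The ranges are about 1-1.5% extra variance at R = 0.5, 5-6% at R = 1 and 19-25% at R = 2. On the standard-error scale, √1.012 to √1.062 is about 0.6-3%, and √1.186 to √1.247 is about 9-12%. Moving the limit from 90 to 104 days changes almost nothing (1.246 against 1.247 at τ = 30, R = 2).

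**4. Primary endpoint.** The Sample Size figure reproduces. With 0.125 against 0.017, two-sided 5%, 80% power and a continuity correction, n is 106 per group. Then 106/0.9 = 117.8, rounded up to 118, or 236 in total. Time since stroke does not enter this calculation.

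**The case against.** The strongest reply is that little follows from either matter. Textbox 1 holds the operative criteria and Study Design is a summary sentence. The windows are nested, so few patients are affected. The dropout criterion on ineligibility refers to the inclusion and exclusion criteria, so a patient at day 99 who meets Textbox 1 is not plainly a dropout. A reader might infer that sites will enrol and then drop the same patient, but the text does not establish that. The two printed rules still disagree.

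A reader might also infer that the mismatch between the windows causes the noise. It does not. The spread from about day 1 to day 90 is common to both rules and is a legitimate eligibility choice. Using one clock would not reduce it.

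It can further be said that model terms for exploratory endpoints belong in a statistical analysis plan, which is not shown. That would answer a complaint about an omission. Here the protocol states a covariate rule, and the stated rule is the problem.

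The proposed covariate is also not assured. Footnote f asks for the first onset, which could mean a first-ever stroke and not the index stroke, and allows the day to be missing. This stands and is dealt with in the fix.

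Finally, the Discussion hypothesises "improving neurological symptoms in patients with small-vessel disease", while the neurological scales are exploratory. A reader might infer a hierarchy error. The aim in Study Design is recurrence prevention and safety, and no confirmatory claim is attached to these scales, so moving one to a higher rank would be a preference.

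**Conclusion.** Both matters hold in limited form. The entry clocks conflict for patients about 91-104 days after stroke (later if diagnosis lagged onset) and need reconciling. Which limit is right is for the sponsor.

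The covariate rule chooses adjustment variables by chance imbalance and so gives up precision on the functional and fatigue scores. Randomisation balances entry time in expectation, so a reader who infers bias in the treatment comparison goes further than the documents allow. The primary endpoint's sample size is not affected.

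The size rests on the assumed exponential recovery and uniform entry. On that basis, entry time alone adds about 1-6% to the variance for total recovery of 0.5-1 residual SD and 19-25% at 2 SD. Any gain from adjusting for the day-0 score is additional and is not quantified here. A larger claim is tempting: if the two covariates together explained 10-30% of the variance in change, adjustment would be worth 1/0.9 = 1.11 to 1/0.7 = 1.43 times the patients. The documents give no such proportion, and the figure pools day-0 score with entry time, so it should not be attributed to the entry window.

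**What to change.** 1. State one entry clock and one limit, of the sponsor's choosing, identically in Study Design and Textbox 1, naming both the start and the end of the interval.
2. For the functional and fatigue scores, replace the significance-triggered rule with prespecified adjustment, in all cases, for the day-0 value of the score and the time from index stroke to day 0.
3. Before relying on the second covariate, confirm that the onset date in footnote f is that of the index stroke, and state how a date with a missing day is handled.

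The cost is two model terms and possibly some incomplete onset dates. No new assessment is needed, provided the index-stroke date is recorded. Recruitment is under way, so a changed entry rule would be an amendment to a running trial, but only 12 of 236 participants had been randomised by November 13, 2024 and no data had been analysed when the article was written.
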